### Outcomes

#### Primary outcomes

The primary outcomes for the study are as follows:Percentage of mothers who know at least three danger signs;Percentage of VHSG volunteers who know six danger signs;Percentage of families who seek care from an appropriate facility;Decreased time between onset of suspected danger signs and referral to appropriate facility;Improved infection prevention behaviors by family, as measured by the proportion of hand washing with soap at key events, calculated as a composite score from the percentage of mothers or caretakers reporting hand washing at the following key events: after going to toilet, before touching newborn, before eating, and after cleaning baby’s bottom;Improved infection prevention and control behavior among health center staff, as measured by the proportion of appropriate hand washing with soap or disinfectant at key points in provision of care to mothers and newborns, calculated as a composite score from: percentage of health center staff reporting hand washing: before patient contact (when they examine mother and newborn), before and after aseptic procedure, after exposure to blood or body fluids, after patient contact (after removing gloves), and after touching patient surroundings.

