#### Primary outcomes

The primary outcomes of the process evaluation are as follows:Percentage of newborns visited by a VHSG volunteer within 24 hours of arriving home,Percentage of newborns visited by a VHSG volunteer on day three of life,Percentage of newborns visited by a VHSG volunteer on day seven of life,Number of VHSG volunteers trained,Number of health center staff trained,Presence of training materials in VHSG equipment, andPresence of training materials in health centers.

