### Trial design

The health center functions as the unit of allocation, with health centers randomized to an intervention start date using a stepped wedge design. The design is principally a matched one, with before and after comparisons for each unit of randomization. On the hypothesis that 16 health centers are recruited, one health center will be assigned to start each month, and randomization will be stratified in order to ensure balance across time points. In this design, all clusters (health centers) receive the intervention in due course (unidirectional crossover) and, in particular, the intervention is never removed once it has been implemented, which allows convenience and alleviates ethical concerns. All cases will be used in the primary analysis, constituting an intent-to-treat approach. Full study enrollment will be completed at 16 months and duration of participation in the intervention will vary based on randomization assignment, with all clusters enrolled with a unidirectional approach and participating for the last six months of the trial.

All health centers in the trial will be included in the intervention, but will be randomized to one of 16 start dates. The center-level intervention will be implemented one stage at a time, progressively over the study period, until all centers have received the intervention. In addition to center level, patient-level data will also be collected. Thus the analysis is divided into center level and patient level, with the patient-level analysis as the primary outcome. All live births occurring in the study area will be eligible, and pregnant women in the last trimester will be recruited from health center catchment areas using the stepped wedge design, where each area will serve initially as control and later as intervention. The study will enroll a target sample size of 1,957 recently delivered women.

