### Analysis plan

The analyses of study data will be performed using the principle of intention-to-treat for the analysis of randomized controlled trials. The exploratory data analysis will be performed for all descriptive statistics, such as means, proportions, variances, and correlation by time and group. Two group (control and intervention) comparison analysis at each time point, across all time points and within each cluster will be performed. One-way crossover design analysis methods will be used for stepped wedge design data, that is, analyses will be performed accounting for potential within-cluster correlation using a random effect model, multilevel model, or generalized estimating equations. Based on each month of the study, we will compare the neonatal mortality rate in those centers that have not yet received the intervention with those in the centers that have. The study hypothesis will be tested on the significance level of alpha = 5 % throughout the analysis. All analyses, summaries, listing, and graphing will be performed on the data, using SAS software (version 9.1 or higher in a Windows environment SAS Institute Inc. Cary, North Carolina, USA). In order to avoid the potential problem of multiple comparisons related to the primary outcomes we plan to apply a Bonferroni correction.

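### The Bonferroni plan names no single comparison per primary outcome to carry the corrected alpha, and Holm would give the same familywise protection with at least as much power

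*Protocol article*

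**What the plan says.** Four places in the protocol article bear on this.

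- **Analysis plan, level and correction.** "The study hypothesis will be tested on the significance level of alpha = 5 % throughout the analysis". The paragraph closes with "In order to avoid the potential problem of multiple comparisons related to the primary outcomes we plan to apply a Bonferroni correction". No divisor is printed.
- **Analysis plan, comparisons.** "Two group (control and intervention) comparison analysis at each time point, across all time points and within each cluster will be performed". The next sentence describes the stepped-wedge analysis proper, which allows for within-cluster correlation through a random effect model, a multilevel model or generalized estimating equations.
- **Primary outcomes (under Outcomes).** "The primary outcomes for the study are as follows", followed by six items. Four concern mothers or families: knowledge of danger signs, care-seeking, time to referral, and hand washing. One concerns village volunteers ("Percentage of VHSG volunteers who know six danger signs") and one concerns hand washing by health center staff.
- **Trial design.** "Thus the analysis is divided into center level and patient level, with the patient-level analysis as the primary outcome".

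**The concern.** A Bonferroni correction protects the family of tests it is applied to. Here that family is the set of primary outcomes, which implies one test per outcome. The plan names three kinds of comparison for the trial data and does not single out one of them as the confirmatory test. The Trial design section adds to the doubt by describing the design as mainly matched, with before-and-after comparison within each center, so a within-cluster contrast could be taken for the main analysis as readily as the overall model estimate. If the choice among comparisons stays open until the data are seen, the error rate for an outcome is no longer 0.83%, and the correction does not deliver what it was included for.

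The second issue is efficiency. Plain Bonferroni gives up power that can be recovered at no cost in error control. The Sample size section uses an undivided 5% level and an exploratory outcome (all-cause newborn mortality), so nothing in the article shows that power was reserved for the correction.

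**Working it through.** The article states no adjusted significance level, so there is no figure of its own to reproduce. The inputs are the 5% level and the Bonferroni rule (Analysis plan), six outcomes (Primary outcomes), 16 centers with one starting per month (Trial design), and three interview rounds (Data collection: third trimester, day 14, day 29). Tests are taken as two-sided, which is an assumption.

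**1. The planned correction, one test per outcome.** Level per test: 0.05/6 = 0.00833. Familywise error if the tests are independent: 1 − (1 − 0.00833)^6 = 4.9%. The planned method works as intended when there is one test per outcome.

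**2. What dividing by six leaves uncovered.** If one outcome can be declared positive on any of k comparisons, each tested at 0.00833, the chance of a false positive for that outcome, treating the comparisons as independent, is 1 − (1 − 0.00833)^k.

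| k | How it arises | False-positive chance, one outcome |
|---|---|---|
| 1 | one named estimate | 0.83% |
| 2 | a choice between two comparisons | 1 − 0.99167^2 = 1.7% |
| 20 | 3 interview rounds + 1 overall + 16 centers | 1 − 0.99167^20 = 15.4% |
| 32 | 15 months with both conditions present + 1 overall + 16 centers | 1 − 0.99167^32 = 23.5% |

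The last two rows are upper illustrations. The comparisons share data and so are not independent, and the article neither defines a time point as a month for the primary outcomes nor says that every outcome is compared in every center.

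**3. Bonferroni against Holm.** Assume each outcome with a real effect has 80% power at two-sided 5%. Its z-statistic then has mean 1.960 + 0.842 = 2.80. The Bonferroni critical value at 0.00833 two-sided is 2.638, so the power per outcome is P(Z > 2.638 − 2.802) = 56%.

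Holm orders the six p-values and compares the smallest with 0.05/6, the next with 0.05/5, then 0.05/4, 0.05/3, 0.05/2 and 0.05, stopping at the first failure. Its first threshold equals Bonferroni's and the later ones are larger, so it rejects everything that Bonferroni rejects. Simulating sets of six z-statistics gives:

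| Situation | Bonferroni | Holm |
|---|---|---|
| No real effect: familywise error, correlation 0 | 4.9% | 4.9% |
| Three real effects: average power | 56% | 60% |
| Six real effects: average power, correlation 0 | 56% | 68% |
| Six real effects: average power, correlation 0.5 | 56% | 67% |

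**4. Level of analysis.** The Trial design sentence makes the patient-level analysis primary, while two of the six primary outcomes are measured on volunteers and on health center staff. The sentence does not say that these two leave the family, but it does not describe them correctly either.

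**The case against.** The case for leaving the plan alone has several parts, and much of it stands.

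- **The 5% level.** A reader might infer that testing at 5% throughout contradicts the Bonferroni correction. It need not. Bonferroni requires an overall level to divide, and 5% reads naturally as that level. Only a literal per-test reading of the word throughout conflicts.
- **Inflated error.** A reader might go on to compute 1 − 0.95^6 = 26.5% familywise error, or 32 × 6 × 0.05 = 9.6 expected false positives. Both describe uncorrected testing of the primary outcomes, which the plan expressly rejects.
- **Size of the family.** A reader might count four outcomes (patient level only) or thirteen (adding the seven introduced by "The primary outcomes of the process evaluation are as follows"). The second list belongs to the process evaluation, and the Trial design sentence removes no outcome. Six is the natural divisor.
- **The comparisons.** The sentence on two-group comparisons follows one on descriptive analysis and may itself be descriptive. Month-by-month comparison is named only for neonatal mortality, which is exploratory. So 32 comparisons per outcome is an inferred upper count and not a stated plan. What remains is that the text does not call these comparisons descriptive and does not name the overall estimate as the test.
- **Holm as preference.** Bonferroni is valid, so Holm improves the plan and corrects no error. The gain depends on how many effects are real and shrinks as fewer are. Bonferroni also gives simple simultaneous confidence intervals, which Holm does not readily do. That is a real cost, though a small one.
- **A separate analysis plan.** One may exist and may settle the contrast. The article's own wording should still be consistent with it.

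**Conclusion.** The point holds as a clarification plus a nearly free improvement. The correction is valid for six outcomes at 0.83% each, but the plan does not say which comparison of each outcome is tested at that level. The correction therefore protects across outcomes and not within one. The size of that gap cannot be fixed from the article: it is nil if only the overall estimate is tested, and at most about 23.5% for one outcome under the independence illustration with 32 comparisons.

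Replacing Bonferroni by Holm keeps the familywise 5% and raises average power from about 56% to about 60% (three real effects) or 67-68% (all six). These figures rest on an assumed 80% power per outcome at two-sided 5%. They show the size of the gain and are not estimates of this trial's power, for which the article gives no basis on any primary outcome. The documents do not support a finding of contradiction or of uncontrolled error.

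**What to change.** Amend the Analysis plan and Trial design sections along these lines:

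1. State that 5% is the familywise level for the six outcomes in the Primary outcomes section.
2. State that each of the six is tested once, through the overall intervention estimate adjusted for time and accounting for clustering by health center.
3. Replace Bonferroni by Holm's step-down procedure.
4. State that the time-point and within-cluster comparisons are reported descriptively, without significance claims.
5. Reword the Trial design sentence so that it gives the level of analysis for each primary outcome, including the volunteer and staff outcomes.

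The cost is wording only: no added data, participants or procedures. Simultaneous confidence intervals are less simple under Holm, and Bonferroni-adjusted intervals can be reported alongside the Holm decisions.

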### Capacity development

From the implementation study, we envisage the following capacity development at the provincial level:Through training and supervision, the intervention health centers will learn a simple approach in improving newborn care based on their existing resources, such as infection prevention control practices, and coordination and follow-up of newborns with VHSGs.Through training and supervision, VHSGs in the intervention clusters will be equipped with better knowledge and effective educational materials for providing health education on newborn health, and will understand and be able to help mothers and families to act faster on newborn referral.Through meetings and updates on the progress of the study, the management of the Takeo Provincial Health Department will be informed and understand the implementation modality of the study.

We envisage the following capacity development at the national level:The National Maternal and Child Health Center (NMCHC), whose director is a member of the Study Advisory Committee, will contribute to the operational modality of the study through sharing the study’s annual progress report, informal interaction with the project staff, and periodic update during NMCHC sub-technical working group meetings.Stakeholders in-country, such as USAID/Cambodia, other United Nations agencies, and NGOs such as Reproductive Health Association of Cambodia (RHAC), Reproductive and Child Health Alliance (RACHA), University Research Corporation (URC), Cooperative for Assistance and Relief Everywhere (CARE) International, and so forth will be apprised of intervention progress through participation in the sub-technical working groups and access to the study publications.The National Institute of Public Health, through the management of the study, will be able to further improve the capacity of the faculty and administrative staff, for example in research, grant management and compliance with trial requirements.

### Data dissemination plan and knowledge transfer

Research results will be shared with all study stakeholders, and promptly discussed with the local health center and village-level participants. Local dissemination meetings with the study populations will be held, including through presentation of the study during Operational Health District monthly meeting and during Provincial Technical Working Group meetings. After the intervention has concluded, a detailed evaluation report of lessons learned will be distributed to relevant partners, along with any intervention materials of interest. Policy briefs will be circulated nationally and internationally to relevant organizations.

Dissemination of study results will also occur at scientific meetings and through publications on the impact of the intervention on neonatal morbidity and mortality rates, behavior change, impact on neonatal care in facilities, referral process and follow-up of neonates, impact on infection control, types of pathogens isolated from neonates clinically diagnosed with sepsis, process outcomes, and lessons learned concerning working with health center providers and VHSG volunteers, supervision, monitoring, and performance; training on danger signs; and social or cultural factors effecting response to specific care recommendations including special care for low birth weight babies and referrals.

It is anticipated that dissemination will result in improved policies and strategies to reduce newborn mortality in Cambodia, especially given the central role of the NMCHC (who determine MNCH national policy) and NIPH in the conduct of the study. The Study Advisory Committee will also facilitate dissemination and integration of translational findings. Study partners at the national level are committed to translating research findings into policy and documenting promising intervention practices for further scale-up. NGO partners supporting other health centers will also be invited to share the results and benefit from technical support from the investigators.

### Ethical approval

The study has been approved by Federalwide Assurance (FWA)-certified institutional review boards (IRBs) in Cambodia and the United States. In Cambodia, the responsible IRB is IRB00003143 - National Ethics Committee Health Research IRB #1 under FWA 00017450 National Institute of Public Health. In the United States, the responsible IRB is IORG0000197 - Tulane University Medical Center under FWA 00002055 Tulane University, with approval through an Institutional Review Board Authorization Agreement.

## Discussion

This study addresses the need to evaluate newborn health approaches linking behavior change in the health center and home environment with improved care-seeking at the community level. The intervention will provide data on how infection prevention control, improved linkages between health centers and community volunteers, and prompt care-seeking will impact newborn health. The results of this study will provide data for policy-level actions on newborn survival in Cambodia, as well as in other settings with similar health outcomes. It will also contribute to the potential scale-up of a linked model of community-facility care for newborns.

### Trial status

This study is currently in the early stages of implementation. Recruitment began 19 February 2015.

## Abbreviations

NICCI: Newborn infection control and care initiative for health facilities to accelerate reduction of newborn mortality
NMCHC: National Maternal and Child Health Center
SMCP: Safe motherhood clinical protocol
VHSG: Village health support group
